**Table 1 Tab1:**
[figure not shown]
Schedule of enrolment, interventions, and assessments

Participants will be invited via email to complete follow-up assessments at 3, 6, 12, and 24months after their enrolment in the study. They will not be dropped from the study unless they explicitly request to withdraw by contacting the research team as indicated in the consent form. Participants who drop out or require ancillary or post-trial care will be provided with local resources (e.g., contact information for crisis lines, emergency departments, family physicians, etc.) and encouraged to create a non-research account with the online program.

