### Confidentiality

Anonymity cannot be guaranteed, due to the use of email addresses (for online accounts and e-gift card compensation) and names to match interview data with online data. At the outset, participant data will be linked via personal information provided. Data from the online workbook will be linked with personal and survey data via unique participant identification numbers. Participants will be informed of these limits to anonymity during the consent process. After all data has been linked and participants have been compensated, personally identifying information (in a master spreadsheet) will be permanently deleted, with the exception of age and sex. This will leave only the anonymized data in an SPSS file. Participant data will be kept completely confidential unless there is (a) acute risk of harm to self or others (e.g., suicidal plans) or (b) court-ordered subpoena/other legal demands for data. If there is a high risk to self or others disclosed during an MI session, participants will be informed that members of the research team may contact local authorities or medical services to prevent harm.

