### Intervention conditions

#### Internet only (IO)

This treatment group will be provided with access to an online workbook (www.gamblingselfhelp.com) based on a paper version mentioned earlier [10] that has demonstrated efficacy in multiple trials [11–14]. It consists of cognitive-behavioral self-help tools to reduce problem gambling. These tools are organized into four modules: self-assessment, goal setting, goal implementation, and goal maintenance. The design of the modules allows for the provision of concise cognitive-behavioral strategies for controlling or abstaining from gambling. The activities within each module may be completed in any order and as many times as desired. None of the activities is mandatory. Participants will have unrestricted access to the site for the entire duration of the study in order to mimic other web resources as much as possible in terms of accessibility.

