#### User data

In addition to the measures described above, user data will also be collected from the workbook website. These data will allow us to examine how much time participants spend on the site and individual modules, as well as which modules are in progress or completed, and the number of times participants logged on to access the online workbook.

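### Participants who need ancillary care while still in follow-up are steered to a non-research account, so their recorded site use may be incomplete in the usage analyses

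*Protocol article*

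**What the plan says.** Four statements in the protocol article bear on this.

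- **Paragraph after Table 1, the rule.** "Participants who drop out or require ancillary or post-trial care will be provided with local resources", and the same sentence has them "encouraged to create a non-research account with the online program".
- **Same paragraph, trial status.** "They will not be dropped from the study unless they explicitly request to withdraw by contacting the research team". Surveys run for two years: "Participants will be invited via email to complete follow-up assessments at 3, 6, 12, and 24months after their enrolment in the study".
- **Intervention conditions, Internet only.** "Participants will have unrestricted access to the site for the entire duration of the study". The section on the interview arm gives that arm the same access.
- **Confidentiality and User data.** "Data from the online workbook will be linked with personal and survey data via unique participant identification numbers", and "user data will also be collected from the workbook website", covering time on site and on modules, module status and number of log-ins.

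Recorded use then enters two analyses. The Data analyses section plans a Pearson correlation of site time with change in gambling spend. It is labelled H3 there, although the usage-outcome hypothesis is H4 in the list of hypotheses. The same section plans unpaired t tests by arm on modules completed and total site time. These are labelled H4 there, although adherence is H5 in the list. Adherence and engagement are also the second of the two specific objectives.

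**The concern.** Ancillary care is named separately from drop-out and from post-trial care, so the rule covers people who are still in the trial. For them the advice serves no stated purpose, because their study account gives the same programme without restriction for the whole period. If they follow it, site time, log-ins and modules may stop accruing under the study number while their survey outcomes keep arriving.

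This would not show up as a missing value. The participant would simply appear to be a light user, so the multiple imputation planned for missing follow-up data would not be triggered. The correlation is unadjusted, so nothing else in the planned analysis would compensate.

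Two results are exposed. The usage-outcome correlation could shift if switchers differ from others in outcome. The adherence comparison could shift if switching is more common in one arm. The interview arm is the only one with a clinician conversation in which a need for care might be noticed, and fewer recorded modules there would work against H5.

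**Working it through.** **Step 1. Does the rule reach retained participants?** Yes, as worded. Ancillary care is listed apart from the other two reasons, and only an explicit request ends participation.

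**Step 2. Is the second account needed for access?** No. Study access is unrestricted throughout.

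**Step 3. Is use on the second account captured?** The article does not say. Linkage runs through participant numbers, and the label non-research suggests that the account lies outside study data. Loss is therefore a reasonable inference and not a stated fact.

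**Step 4. Effect on the correlation.** The plan states no figure to reproduce. These inputs are all assumed:

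- share switching: 5%, 10% or 20%
- fraction of their time still recorded: 25%, 50% or 75%
- their mean improvement: 0.5 SD worse, equal, or 0.5 SD better
- their true use: equal to others, or 1 SD heavier on the log scale
- latent correlation of log time with improvement: 0 or 0.2

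Model: site time = exp(0.8 × X), with X standard normal (plus 1 for switchers in the heavier-use case). Recorded time is true time × fraction kept for switchers, and true time for everyone else. Bias is the Pearson r from recorded time minus the r from full time, with 400,000 simulated participants per scenario. Time is left untransformed, because the transformations in Data analyses are planned for the primary outcome variables and site time is not one.

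| Switchers' improvement | Bias in r, 10% switch, half of time kept |
|---|---|
| 0.5 SD less | +0.02 to +0.06 |
| equal | -0.005 to +0.016 |
| 0.5 SD more | -0.02 to -0.04 |

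Across all scenarios reported (10% switching with each fraction kept, and 5% and 20% switching with half kept) the bias ran from about -0.07 to +0.08.

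**Step 5. Effect on the test when use and outcome are truly unrelated.** Take n = 2 × 108 = 216, the sample before attrition is added. With Fisher's transformation, z = atanh(r) × √(216 - 3), and the rejection probability is P(Z > 1.96 - z) + P(Z < -1.96 - z). These cases use equal true use and 0.5 SD less improvement among switchers.

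- 10% switch, half kept: r = 0.021, z = 0.31, rejection about 6%
- 10% switch, a quarter kept: r = 0.035, z = 0.51, rejection about 8%
- 20% switch, half kept: r = 0.046, z = 0.67, rejection about 10%

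The nominal rate is 5%. Direct simulation at n = 216 gave 7%, 8% and 10%.

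**Step 6. Effect on the adherence comparison.** If switchers use the site as much as others, recorded mean time in an arm falls by share × fraction lost.

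- 10% switching in the interview arm only, half lost: 0.10 × 0.50 = 5% of that arm's mean
- 5% and 20% switching, half lost: 2.5% and 10%
- the same loss in both arms: both means, and so their difference, shrink by that percentage

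**The case against.** The strongest reply is that the sentence is only loosely worded. Switching is encouraged and not required, the study account stays open, and a participant with unrestricted access has little reason to register again. The natural purpose of the sentence is to tell people who have left, or whose trial is over, that the site remains available. Few retained participants may be reached. Endorsing item 9 of the PHQ-9 triggers an automated message with no contact from the team, and the text on risk disclosed in an interview concerns authorities and medical services. Neither mentions a new account. The Confidentiality section also says email addresses are used for online accounts, so a second account might be traceable while identifiers are held. Usage is a secondary matter, and a correlation between use and outcome is observational in any case.

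Most of this stands, and it limits the size of the point. It does not remove the conflict: the rule as written includes retained participants, and the article provides no linkage for the second account.

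A reader might go further and infer that later use is lost and that the correlation is thereby pushed towards the hypothesis. The documents do not support either step. They nowhere say that the second account replaces the first or cannot be linked. They also do not say that people needing ancillary care reduce their gambling less. The resources named, such as crisis lines and emergency departments, point to acute distress, which is not the same as a poor gambling outcome. If the extra care helps, the bias reverses. Large inflation of the error rate appears only with near-deterministic selection of the worst-faring, full uptake of the second account and log-transformed time. With untransformed time and that strong selection, 10% switching and losing half their time gives about 14%. Milder selection or 50% uptake brings it to 5-7%.

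**Conclusion.** The point holds in a limited form. The paragraph after Table 1 steers some participants who remain in follow-up to an account outside the study, although they already have full study access, and this may leave their use under-recorded in two planned analyses. The primary frequency, severity and expenditure comparisons do not use site time and are unaffected.

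The bias is probably small: below about 0.1 in r in every scenario reported, and a few per cent of mean recorded time, up to 10%, in an affected arm. Its direction is uncertain. It runs towards the usage-outcome hypothesis if switchers improve less than average, away from it if they improve more, and against H5 if need is noticed more often in the interview arm. The share switching, the uptake, the time lost and the outcomes of switchers are all assumptions, because the documents give none of them. The case for acting is that the gap is avoidable at almost no cost.

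**What to change.** Reword the sentence after Table 1 so that the advice to open a non-research account applies only to participants who have withdrawn and to the period after the 24-month assessment. Alternatively, keep the advice and state that use on such an account will be linked to the participant number for anyone still in follow-up. The provision of local resources is unchanged for all three groups.

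For switches already made, log the date and run the usage-outcome correlation and the adherence t tests with and without those participants as a sensitivity check.

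The cost is one sentence in the protocol, a matching edit to any email template, an ethics submission for the amendment, and a short log. Participants lose nothing, since the study account gives the same programme. Recruitment was still open at protocol version 3, so much of the follow-up can still be protected.

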### Intervention conditions

#### Internet only (IO)

This treatment group will be provided with access to an online workbook (www.gamblingselfhelp.com) based on a paper version mentioned earlier [10] that has demonstrated efficacy in multiple trials [11–14]. It consists of cognitive-behavioral self-help tools to reduce problem gambling. These tools are organized into four modules: self-assessment, goal setting, goal implementation, and goal maintenance. The design of the modules allows for the provision of concise cognitive-behavioral strategies for controlling or abstaining from gambling. The activities within each module may be completed in any order and as many times as desired. None of the activities is mandatory. Participants will have unrestricted access to the site for the entire duration of the study in order to mimic other web resources as much as possible in terms of accessibility.

#### Internet plus motivational interview (IMI)

This treatment group will be provided with the same access to the online workbook as those in the IO group, plus one brief (i.e., 30- to 60-min) motivational interview delivered digitally through an online audioconferencing platform (i.e., Microsoft Teams) within the first two weeks of study enrolment. In the event that participants have difficulties with Microsoft Teams, interviews will be conducted via telephone. Participants who refuse the motivational interview will not be compensated with the initial gift card, but will be retained in this group and followed up with in accordance with an intention-to-treat approach (ITT). Motivational interviewing involves the assessment of a client’s readiness for change, followed by the facilitation of behavioral change by exploring ambivalence, building commitment, and eliciting reasons for change [25]. Clinical psychology graduate students will be trained to conduct the motivational interviews and will be compensated with clinical credit hours. All calls will be digitally recorded. Twenty percent of the calls will be assessed for treatment fidelity using a treatment adherence checklist, and they will be rated by two independent raters for reliability. The adherence checklist covers a number of elements that are essential to include (e.g., asking for commitment) and not include (e.g., providing unsolicited advice) during the interview sessions.

### Eligibility assessment

#### Demographics

A variety of demographic questions used in previous gambling trial studies will be asked to screen for eligibility and gather descriptive information in regards to age, sex, education level, income, occupation, ethnicity, marital status, and types of gambling they engage in. They will also be asked whether or not they are currently receiving treatment for their gambling and if they have in the past.

#### Gambling severity

The PGSI [20] will be used to screen for gambling problems prior to study commencement. The PGSI is a 9-item scale used to assess problem gambling severity. Respondents answer a series of questions related to their gambling on a 4-point scale ranging from “never” to “almost always,” and total scores range from 0 to 27. While many prior trials have used a PGSI score of 3 as a cutoff, Currie, Hodgins, and Casey [26] determined that a cutoff score of 5 better differentiates low- from moderate-risk behavior in terms of gambling expenditures. PGSI scores have been shown to correlate highly with other measures of gambling severity (*r* = .83), such as the National Opinion Research Center DSM-IV Screen for Gambling Problems (NODS). Additionally, the PGSI has demonstrated good internal consistency (*α* = .84) [20].

### Baseline and follow-up assessments

#### Primary outcomes

##### Gambling frequency and expenditures

Prospective participants will also be asked to estimate the average number of hours they have gambled per month and per gambling session over the last three months, as well as the average amount of money they won or lost per month and per gambling session. These 3-month retrospective self-report questions were adapted from the Gambling Participation Instrument (GPI) [27].

##### Gambling severity

In addition to gambling frequency and expenditures, gambling severity will also be assessed. The NODS [28] is a 17-item measure that uses DSM-IV criteria to assess gambling problems. The 3-month version of the NODS has been previously validated as an outcome measure for gambling intervention research, demonstrating good internal consistency (*α* = .87) [29]. It also correlates highly with other measures of gambling severity (*r* = .86) and moderately with number of days gambled and number of dollars spent (*r* = .50) [30].

#### Secondary outcomes

##### Depression symptoms

The Patient Health Questionnaire-9 (PHQ-9) [31] is a 9-item scale that measures symptoms of depression over the past two weeks. Item response options range from 0 (not at all) to 3 (nearly every day), yielding total scores that range from 0 to 27. The PHQ-9 has shown good internal consistency (*α* = .89) [31]. Note that participants who endorse question 9 on the PHQ-9 (i.e., thoughts that they would be better off dead or hurting themselves in some way) will be directed to an automated response at the end of the survey; this response will encourage these participants to consult a resource (e.g., family physician) or contact a crisis helpline via phone numbers provided to them. They will be explicitly informed that contact from the research team will not follow the automated response.

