### Participant recruitment and randomization

Participants will be recruited via targeted internet advertisements (i.e., “Are you concerned about your gambling? Study includes free and confidential online help for your gambling”). These advertisements will be distributed online (e.g., Facebook; Kijiji; YouTube; Google; Twitter; Reddit) to media users across Canada. To meet inclusion criteria, participants must (a) be a Canadian resident; (b) be 18 years of age or older; (c) have gambled at least once within the last month; (d) score 5 or more on the Problem Gambling Severity Index (PGSI) [20]; and (e) not currently be involved in treatment for their gambling. As with most prior gambling intervention trials, use of psychiatric medication will not be an exclusion criterion, but will not be assessed or monitored in this study. Prospective participants will be excluded if they are unable or unwilling to (a) provide their phone number and email address or (b) access the online program to create an account.

Individuals who are interested will be automatically redirected from a social media advertisement to an online eligibility screening questionnaire on Qualtrics. Those who are found to be ineligible will be thanked for their interest and directed to alternative resources for gambling help without any contact from the research team. Those who meet eligibility criteria will be automatically prompted to provide consent and contact information within Qualtrics, and then complete the baseline assessment. Qualtrics will be monitored daily for completed surveys that meet eligibility criteria and indicate consent. Eligible participants will be randomized by the research team to one of the two treatment groups and notified of their group assignment via email. Those selected to receive a motivational interview will also be invited to schedule their session. As previously mentioned, participants will not receive the initial compensation until the aforementioned steps have been completed. Those who complete at least one but not all of these steps will be sent a maximum of two reminder emails. Eligible participants can choose to be informed of the trial results via email upon its completion. Regardless, any publications and presentations resulting from this trial will be agreed upon by all investigators.

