#### Anxiety symptoms

The Generalized Anxiety Scale-7 (GAD-7) [32] is a 7-item scale that measures symptoms of anxiety over the past two weeks. Each item is responded to using a 4-point Likert scale, and total GAD-7 scores range from 0 to 21. The GAD-7 has demonstrated excellent internal consistency (*α* = .92) [32].

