#### General psychological distress

The Kessler Psychological Distress Scale-10 (K-10) [33] is a 10-item scale used to assess nonspecific psychological distress-related symptoms over the past four weeks. Response options span a 4-point scale ranging from “none of the time” to “all of the time,” and total scores range from 0 to 40. The K-10 has demonstrated high internal consistency (*α* = .78) [33].

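### The PHQ-9 item 9 safety message appears only at the end of the survey, so a participant who endorses the item and leaves early would miss it unless the PHQ-9 comes last

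*Protocol article*

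**What the plan says.** Under Depression symptoms, the protocol article describes one response to an endorsed item 9. The participant "will be directed to an automated response at the end of the survey". The message recommends consulting a resource such as a family physician, or calling a crisis line whose number is supplied. Participants are also told that "contact from the research team will not follow the automated response".

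Three other provisions bear on safety or on incomplete participation:

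- Confidentiality has a procedure for acute risk in the interview: "If there is a high risk to self or others disclosed during an MI session", the team may involve local authorities or medical services.
- Participant recruitment and randomization covers people who stop partway through enrolment: "Those who complete at least one but not all of these steps will be sent a maximum of two reminder emails".
- The text below Table 1 covers people who leave the study: "Participants who drop out or require ancillary or post-trial care will be provided with local resources", with crisis lines among the examples.

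The order of the instruments within a survey is not stated. Table 1 is a schedule of assessments and is not reproduced in the text at hand.

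**The concern.** As described, the message depends on reaching the end of the survey as well as on the answer to item 9. These are two separate conditions. A participant can meet the first and fail the second by closing the browser.

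The assessments are completed online without supervision, and the article's Background names suicidality among the problems that accompany gambling disorder. Because the team has ruled out follow-up contact after item 9, nothing described would later make up for a message that was not displayed. What is at stake is participant safety. No estimate, test or error rate in the trial depends on it.

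**Working it through.** The article gives no figure to reproduce, so the check is a reading of the relevant sections against each other, plus a count of what could follow item 9.

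**1. What *survey* refers to.** Participant recruitment and randomization says that Qualtrics is checked daily for completed surveys. Participant validation places the VPN block and reCAPTCHA in each survey. In both places the word means the whole online assessment. Participant validation also once calls the IEUQ, a single questionnaire, a survey. So the whole-assessment reading is the more natural one, but it is not certain. If the word meant only the PHQ-9, item 9 is the last of its nine items and there would be no gap.

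**2. What could follow item 9.** Item counts come from the instrument descriptions. The NODS "is a 17-item measure that uses DSM-IV criteria to assess gambling problems", the GAD-7 "is a 7-item scale that measures symptoms of anxiety over the past two weeks", and the K-10 "is a 10-item scale used to assess nonspecific psychological distress-related symptoms over the past four weeks". The AUDIT-C has 3 items and the IEUQ 15. I assume that the IEUQ is given at follow-up only, since it rates the workbook.

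| Position of the PHQ-9 | Scale items after it, baseline | Scale items after it, follow-up |
|---|---|---|
| Last | 0 | 0 |
| Order of the article's headings (not established as the survey order) | 7 + 10 + 3 = 20 | 20 + 15 = 35 |
| First | 17 + 7 + 10 + 3 = 37 | 37 + 15 = 52 |

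If the PHQ-9 came first, the gambling frequency and expenditure questions would follow it as well. The table bounds how much survey could remain after item 9. It does not say how many people stop there.

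**3. Whether another route catches the case.**

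- *Interview procedure.* It is triggered by disclosure in a motivational interview. Only the internet-plus-interview arm has one, and a survey answer does not trigger it.
- *Reminder emails.* They are triggered by unfinished enrolment steps, and nothing links them to item 9.
- *Local resources.* These go to people who drop out or need ancillary or post-trial care. The same paragraph says that participants stay in the study unless they explicitly ask to withdraw, so leaving one survey early is not dropping out.
- *Daily check of Qualtrics.* It looks for completed surveys.

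None of the four is triggered by item 9 or by an unfinished survey.

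**4. Whether break-off is contemplated.** Ethical approval and compensation pays CAD $30 for each follow-up assessment completed in full. That allows for partial completion, and it also gives participants a reason to finish.

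**The case against.** The strongest reply is that the point turns on something the reader cannot see. If the PHQ-9 is last, nothing needs changing. Item order and survey screens are details that an article leaves to the full protocol, and Data Availability says that study materials can be requested. The second reading of *survey* would also remove the gap. This much stands, and it is why the point is conditional. It does not dispose of the point, because the article did not merely leave the placement out: it states where the message appears.

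It is also fair that safety is not otherwise neglected. There is a triggered message, an honest statement that no contact follows, ethics approval, and a payment that encourages completion.

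A reader might infer three stronger things that the documents do not support:

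- *That participants have no access to crisis resources.* Resources are offered on drop-out, and the consent material and survey screens, which may carry helpline numbers, are not shown.
- *That a number of missed messages can be calculated.* Neither the endorsement rate nor the break-off rate is given. The planned 270 is also the wrong base at baseline: according to Participant recruitment and randomization and Blinding, randomization follows the baseline assessment, so people who abandon baseline are not among the 270. At follow-up, people who leave partway may already be counted in the 20% attrition allowance.
- *That the internet-only arm is treated worse.* As described, the survey message is the same in both arms. The interview is an additional occasion for disclosure, not a different response to item 9.

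**Conclusion.** The point holds in conditional form. The only response to item 9 that the article describes is tied to reaching the end of the survey. If *survey* means the whole assessment and any instrument follows the PHQ-9, a participant who endorses item 9 and leaves early would not see it. If the PHQ-9 is last, or *survey* means the PHQ-9 alone, there is no gap.

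The number of people affected cannot be estimated from the document. What can be bounded is the remaining survey: 0 to 37 scale items at baseline and 0 to 52 at follow-up, the latter assuming that the IEUQ is given at follow-up only. Sample size, error rates and planned analyses are not affected. This is a cheap improvement to participant safety, not an error in the statistical plan.

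**What to change.** First check the order of the instruments in the live surveys. If the PHQ-9 is last in each, change nothing.

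Where it is not last, show the existing message on leaving the PHQ-9 page whenever item 9 is endorsed, and again at the end. Do this identically in both arms and in all remaining baseline and follow-up surveys. Keep the message content and the no-contact policy as they are. Record the date of the change. Do not move the gambling questions or the NODS: showing a message does not require it, and reordering primary outcome instruments in an ongoing longitudinal trial could itself shift answers between waves.

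The change can still do some good. At protocol version 3 (19 October 2021) recruitment was planned to run to about 31 March 2022, with follow-up to 24 months.

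The cost is display logic in up to five surveys (baseline and 3, 6, 12 and 24 months) and a short ethics amendment, which Ethical approval and compensation requires for changes to study procedures. There are two downsides. A few participants may stop when they see the message, and it may slightly influence answers to scales that come after it. Identical use in both arms limits bias between arms, but a small effect on change over time in those later scales remains possible, which is why the date should be recorded.
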